| Study design:      | 
The study will be a prospective, randomised, open-label, blinded endpoint (PROBE), phase 3 parallel group superiority trial, with covariate adjusted randomisation and adaptive sample size re-estimation.
 
Study population - ischaemic stroke patients with large vessel occlusion presenting to hospital within 24 hours of symptom onset.
 
Patients will be required to have a large vessel occlusion on baseline CT angiography (CTA) or MR angiography (MRA). LVO will be defined as 'potentially retrievable' thrombus at one or more of the following sites: intracranial and/or extracranial internal carotid (ICA), middle cerebral artery (MCA) first segment (M1) and proximal second segment of middle cerebral artery (M2). Endovascular thrombectomy will be allowed but is not mandatory. Additionally, patients must
 |

|                            |                                                                                                                                                                                                                                                                                                                                                                                                                                                                                                                                                                                                                                                                                                                                                                                                                                                                                                                                                                                                                                                                                                                                                                                                                                                                                                                                                                                                                                                                                                                                             |

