## 2. Background

Ischaemic stroke is the leading cause of adult disability in the world. The current standard of care for treatment of patients with acute ischaemic stroke is intravenous recombinant tissue plasminogen activator (tPA, or alteplase), although its use currently remains restricted to less than 4.5 hours from symptom onset. Presently, only 13% of ischaemic stroke patients in Australia receive alteplase, partly due to the time window restriction. Additionally, alteplase performs relatively poorly in patients with a large vessel occlusion (LVO). Despite availability of alteplase, stroke patients with LVO face a devastating outcome due to the large area of brain tissue affected, resulting in >50% of patients dead or highly disabled at 3 months. However, recent trials have shown that endovascular clot retrieval or thrombectomy (EVT) results in at least a doubling of the odds of disability-free survival, compared to treatment with alteplase alone. It is therefore no surprise that there has been worldwide enthusiasm to translate EVT into routine practice. However, endovascular thrombectomy requires considerable operator expertise and infrastructure, so is limited to high volume stroke centres (which also ensures lower complication rates). This means there are inevitable delays in LVO patients receiving EVT, particularly in rural and regional centres, but also in large cities where inter-hospital transfers can be slow. Intravenous thrombolysis given prior to transfer to a thrombectomy capable centre ('drip and ship') may lead to vessel recanalisation in transit and negate the need for thrombectomy. However, alteplase only leads to recanalization prior to thrombectomy in 10% of patients. Further, its use is currently restricted to <4.5 hours after symptom onset.

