## Reperfusion at 24hr with 0.25 mg/kg TNK

[figure not shown]

The benefit of identifying ischemic tissue and salvageable tissue prior to reperfusion therapy and by excluding mimics using CTP was highlighted by a subsequent phase II tenecteplase trial (ATTEST), which enrolled patients via standard clinical criteria. ATTEST was negative for the primary outcome. Although ATTEST did not use CTP to select patients, fortunately, CTP was still performed. When the ATTEST data was pooled with our Australian TNK trial, only 34% of ATTEST patients had salvageable tissue meeting 'target mismatch' criteria on CTP (explaining the differing results). In the pooled data, there was a substantial clinical benefit over alteplase in patients treated with tenecteplase who had salvageable tissue (return to all usual activities [mRS 0-1] occurred in 35% tenecteplase vs 22% alteplase-treated patients), *with a lower brain haemorrhage rate*.

The recent EXTEND-IA TNK trial, also by our group, showed that 0.25mg/kg tenecteplase was more effective than the standard stroke thrombolytic drug alteplase in patients treated up to 4.5 hours from symptom onset at opening large vessel occlusions prior to thrombectomy in patients who met target mismatch criteria on CTP. The primary outcome of reperfusion at the initial angiogram occurred in 22% of tenecteplase versus 10% of alteplase patients ( $p=0.02$ ). Thus, *1 in 5 LVO patients treated with tenecteplase did not require subsequent thrombectomy* and the number needed to treat with tenecteplase rather than alteplase to prevent one thrombectomy was nine. Although all patients with persisting LVO still went on to thrombectomy, tenecteplase was also associated with improved functional outcome at 90 days (common odds ratio 1.7, 95%CI 1.0-2.8,  $p=0.037$ , Figure 3). This emphasises the benefits of earlier reperfusion with tenecteplase.

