### **6.4 Feasibility**

We are uniquely well-placed in the international stroke trials space to rapidly address this urgent knowledge gap and implement substantive changes in clinical practice. We have built an established network of collaborating hospitals across Australia, New Zealand, Taiwan, Korea, Canada, Spain, Finland, Sweden and the UK to recruit acute stroke patients into acute therapy trials. These sites have participated in a number of our trials including TASTE, EXTEND, and EXTEND-IA. Further, we now have a large network of rural/regional telestroke sites in Australia that are actively enrolling in trials such as TASTE and EXTEND-IA TNK. This is important as we expect that >50% of patients recruited in ETERNAL will be 'drip and ship', and, that the group with delays to thrombectomy may stand to gain more benefit from a more effective IV thrombolytic given prior to transfer. Recruitment is expected to take 5 years.

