### 7.2.2 Day 1 (24 +/- 6 hours post treatment administration)

**Imaging:** All patients will have MRI (Including DWI, FLAIR SWI/GRE, PWI, and MRA) or, if unable to have MRI, multimodal CT (NCCT with CTA and CTP) at 24 hours post treatment to assess for reperfusion, ICH, infarct growth, and recanalisation.

For all patients who undergo thrombectomy, all DSA imaging will also be required to be uploaded to the ETERNAL eCRF.

Any additional patient imaging acquired during their hospital stay will also be required to be uploaded. Such imaging may include additional NCCT if there is an adverse event or change in neurological status.

**Clinical assessments:** Neurological assessment (NIHSS) will be performed at 24hrs by an accredited observer who is blind to acute treatment and imaging findings.

**Adverse Events:** All patients will be asked to report adverse events (refer to Section 8).

**Concomitant medications:** All concomitant medications will be recorded.

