## Secondary Outcomes

### Efficacy

- Proportion of patients achieving early clinical improvement (reduction in acute – 24 hour NIHSS score of  $\geq 8$  or 24 hour NIHSS 0-1).
- Proportion of patients with Modified Rankin Scale 0-2 at 3 months
- Ordinal analysis of mRS at 3 months
- Proportion of patients with TICI 2b/3 on initial DSA run prior to thrombectomy

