## **12.5 Statistical analysis**

The analysis will be conducted following intention-to-treat principles. All outcomes and analyses are prospectively categorized as primary, secondary or exploratory. Differences in all endpoints between the 2 arms of the study will be tested independently at the two-tailed 0.05 level of significance. All estimates of treatment effects will be presented with 95% confidence intervals. No formal adjustments will be undertaken to constrain the overall type I error associated with the secondary and exploratory analyses. Their purpose is to supplement evidence from the primary analysis to more fully characterise the treatment effect. Results from the secondary analyses will be interpreted in this context. Descriptive statistics will be generated for each of the measures used in study.

The primary outcome will be analysed using modified Poisson regression with modified Rankin Scale (mRS) 0-1 (no disability) or return to pre-morbid mRS at 3 months as the dependent variable, treatment arm as an independent variable, and age, baseline NIHSS score, and randomisation-to-groin puncture time (categorized as no EVT, <2 hours, and >2 hours) as treatment covariates. Treatment effect will be presented as adjusted Risk Ratio with corresponding 95% confidence interval (95%CI).

The analyses of dichotomous secondary efficacy and safety outcomes will be conducted using modified Poisson regression with achieving the respective outcome as the dependent variable, treatment arm as an independent variable, and age, baseline NIHSS score, and randomisation-to-groin puncture time (categorized as no EVT, <2 hours, and >2 hours) as treatment covariates. Treatment effects will be presented as adjusted Risk Ratios with corresponding 95% confidence interval (95%CI).

Protocol Number: UOM2102

Protocol Title: ETERNAL LVO

For the ordinal analysis of the day 90 mRS, an ordinal logistic regression analysis model or an assumption-free Generalized OR model analysis will be undertaken on the full range (0-6) of the scale depending on whether the proportional odds assumption is satisfied.

Exploratory outcome analyses will be carried out according to standard statistical principles for comparison of parametric or non-parametric distributions as appropriate.

The details of the statistical analysis will be summarized in a separate Statistical Analysis Plan prior to the lock of the trial data.

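### TICI 2b/3 on the first DSA run can be seen only in patients who reach angiography after randomisation; the upload rule and the no-EVT covariate can distort it, by an amount and in a direction the protocol does not fix

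*Protocol*

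**What the plan says.** Section 12.2 (Secondary Outcomes, Efficacy) defines the outcome as the "Proportion of patients with TICI 2b/3 on initial DSA run prior to thrombectomy"; the Synopsis has the same outcome. No section states how a patient without an angiogram is counted. Section 12.5 says that "The analysis will be conducted following intention-to-treat principles" and leaves details to a separate analysis plan.

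Four statements bear on who has an angiogram:

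- Synopsis, Study design: "Endovascular thrombectomy will be allowed but is not mandatory".
- Section 2: thrombolysis given before transfer "may lead to vessel recanalisation in transit and negate the need for thrombectomy".
- Section 6.4: "we expect that >50% of patients recruited in ETERNAL will be" drip-and-ship patients, so a delay between lysis and angiography is the expected setting.
- Section 7.2.2: "For all patients who undergo thrombectomy, all DSA imaging will also be required to be uploaded to the ETERNAL eCRF".

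The closing line of the Safety list in Section 12.2, and Section 12.5, apply one model to all dichotomous secondary outcomes: modified Poisson regression with age, baseline NIHSS and randomisation-to-groin-puncture time (no EVT, under 2 hours, over 2 hours). The effect measure is the adjusted risk ratio.

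**The concern.** There are three linked problems.

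1. **Selection.** A TICI score exists only if an angiogram was done. Whether it was done is settled after randomisation, and by the protocol's own rationale it can depend on whether the drug worked. A comparison confined to patients with DSA is no longer the randomised comparison.
2. **Data collection.** Read literally, the DSA upload sentence in Section 7.2.2 leaves out a patient whose first run shows an open vessel and who therefore has no thrombectomy. That patient is a success on this outcome. An analysis plan cannot restore images that were never collected.
3. **Adjustment.** The no-EVT category is fixed after randomisation. Here it mixes patients who have no TICI score with, possibly, patients whose vessel was open on the first run. In the second case the model conditions on something close to the outcome.

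At stake is the interpretation of the only listed efficacy outcome that measures reperfusion before thrombectomy.

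**Working it through.** **Inputs.** The protocol gives no expected rate, power or sample size for this outcome; the 740 patients are for the primary outcome. Section 2 reports that in the earlier tenecteplase trial "reperfusion at the initial angiogram occurred in 22% of tenecteplase versus 10% of alteplase patients". I use 22% and 10% as assumed true rates of early opening. As a check, 1/(0.22 − 0.10) = 8.3, which rounds up to the nine patients per thrombectomy avoided that Section 2 reports. Without selection, the difference is 12.0 points and the risk ratio (RR) is 2.20. All selection rates below are my assumptions.

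**Step 1: only patients with DSA are analysed.** Let p be the true opening rate, f the share of opened vessels that never have DSA, and g the same share for unopened vessels. The observed rate is p(1−f) / [p(1−f) + (1−p)(1−g)]. With f equal in both arms and g = 0:

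| f | Tenecteplase | Control | Difference | RR |
|---|---|---|---|---|
| 0.25 | 17.5% | 7.7% | 9.8 points | 2.27 |
| 0.50 | 12.4% | 5.3% | 7.1 points | 2.35 |
| 0.75 | 6.6% | 2.7% | 3.9 points | 2.44 |

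The absolute difference shrinks, the odds ratio stays at 2.54, and the planned measure, the RR, rises slightly.

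**Step 2: patients without DSA count as failures.** The rates become p(1−f). At f = 0.25, 0.50 and 0.75 the differences are 9.0, 6.0 and 3.0 points, and the RR stays at 2.20.

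**Step 3: selection differs by arm, DSA-only analysis.**

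- g = 0, f = 0.50 on tenecteplase and 0.25 on control: 12.4% vs 7.7%, RR 1.61. Reversed: 17.5% vs 5.3%, RR 3.32.
- f = 0.25 in both arms, g = 0.2 on tenecteplase and 0.4 on control: 0.165/0.789 = 20.9% vs 0.075/0.615 = 12.2%, RR 1.71. Reversed: 0.165/0.633 = 26.1% vs 0.075/0.795 = 9.4%, RR 2.76.

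The RR can therefore move either way.

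**Step 4: the no-EVT covariate.** To isolate it, assume everyone has DSA and use two bins (EVT, no EVT), leaving out age and NIHSS. Let h be the share of opened vessels classed as no EVT and d the share of unopened vessels without EVT, equal in both arms. The Poisson point estimate solves Σ[a − m·RR·n_T/(RR·n_T + n_C)] = 0 over the bins. Here a is tenecteplase successes, m is all successes, and n_T and n_C are the patients in the bin.

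Example with h = 1, d = 0.05. In the no-EVT bin, tenecteplase has 0.22/(0.22 + 0.78×0.05) = 0.22/0.259 = 84.9%. Control has 0.10/(0.10 + 0.90×0.05) = 0.10/0.145 = 69.0%. The EVT bin contains no successes, so the adjusted RR is 1.23.

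| h | d | Adjusted RR (unadjusted 2.20) |
|---|---|---|
| 1.0 | 0.05 | 1.23 |
| 0.9 | 0.05 | 1.35 |
| 0.9 | 0.15 | 1.65 |
| 0.5 | 0.15 | 2.05 |
| 0 | 0.05 or 0.15 | about 2.2 |

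The result depends on how a patient who is punctured but not treated is binned. The protocol does not say.

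**The case against.** A reader might infer that patients without DSA drop out and that the comparison is therefore biased against tenecteplase. The documents support neither statement in general. No DSA-only denominator is stated, the principle is intention to treat, and the counting rule may sit in the analysis plan, which is not at hand. On direction, Step 1 shows that equal selection shrinks the absolute difference but not the planned RR, and Step 3 needs arm-specific rates that the documents do not contain.

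Further objections carry weight:

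- No thrombectomy does not mean no DSA. In the earlier trial the successes were seen on the first angiogram. An open vessel on the first run counts here too, so only opened vessels that never have DSA are lost.
- The 22% and 10% come from a trial within 4.5 hours against alteplase, with few transfers. This trial runs to 24 hours and its control arm includes no lysis.
- Section 7.2.2 also asks for any additional in-hospital imaging to be uploaded. A DSA without thrombectomy could be read into that, although the example given there is a further non-contrast CT.
- Reperfusion and recanalisation at 24 hours, from imaging planned for all patients, do not depend on DSA. They are exploratory and measure a later time.

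What stands against these objections: angiography is a post-randomisation event that treatment can affect, the DSA upload sentence names the wrong group for this outcome, and the protocol itself fixes the covariate.

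**Conclusion.** The point holds in limited form. As written, the protocol lets post-randomisation selection and a post-randomisation covariate distort this secondary outcome. Size and direction depend on the effect scale and on selection rates that the documents do not give. With equal selection of 25% to 75% of opened vessels, the absolute difference falls from 12.0 to between 9.8 and 3.9 points, while the RR goes from 2.20 to between 2.27 and 2.44. The clearest distortion is the covariate: if half to all of the opened vessels are classed as no EVT, the adjusted RR is 1.23 to 2.05 instead of 2.20; if none are, it stays at about 2.2. All these figures illustrate a range under assumed rates and are not predictions for this trial. The outcome is secondary, and neither the primary outcome nor the sample size is affected by this point.

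**What to change.** 1. For this outcome, drop randomisation-to-puncture time from the model and adjust for age and baseline NIHSS only. This costs a change of wording.
2. In Section 7.2.2, require upload of every DSA, whether or not thrombectomy follows. This costs one sentence and few extra files.
3. Make the main comparison in all randomised patients, with a fixed rule that patients without DSA count as not reperfused. Add one eCRF item for the reason DSA was not done. Present the DSA-only proportion as descriptive.
4. Add a sensitivity analysis that counts as successes patients whose vessel was open on imaging before angiography. It should not be the main analysis: the protocol requires no such imaging, and in an open-label trial it would be ordered at the discretion of unblinded clinicians.

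The downside is that patients never sent for EVT, and reopened vessels without imaging, count as not reperfused. The absolute difference is then understated, and the RR is too if such losses are more common on tenecteplase. For example, f = 0.50 against 0.25 gives 0.22×0.50 = 11.0% vs 0.10×0.75 = 7.5%, RR 1.47. The sensitivity analysis and the recorded reasons let a reader judge how far this matters.

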### Safety

- Proportion of patients with symptomatic intra-cerebral haemorrhage (sICH) defined as: parenchymal haematoma type 2 (PH2) within 36 hours of treatment combined with neurological deterioration leading to an increase of  $\geq 4$  points on the NIHSS from baseline, or the lowest NIHSS value between baseline and 24 hours
- Proportion of patients with death due to any cause
- Proportion of patients with Modified Rankin Scale (mRS) 5-6 at 3 months (severe disability or death).

All secondary and safety outcomes will also be analysed adjusted for: age, NIHSS, randomisation time to groin puncture time in bins, including a bin for no EVT performed

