| Study endpoint:     | 
Primary Outcome
 
The proportion of patients with Modified Rankin Scale (mRS) 0-1 (no disability) or return to baseline mRS (if baseline premorbid mRS =2) at 3 months.
 
Secondary Outcomes
 
Efficacy
 
 
• Proportion of patients achieving early clinical improvement (reduction in acute – 24 hour NIHSS score of ≥8 or 24 hour NIHSS 0-1).
 
• Proportion of patients with Modified Rankin Scale 0-2 at 3 months
 
• Ordinal analysis of mRS at 3 months
 
• Proportion of patients with TIC1 2b/3 on initial digital subtraction angiography run prior to thrombectomy
 
 
Safety
 
 
• Proportion of patients with symptomatic intra-cerebral haemorrhage (sICH) defined as: parenchymal haematoma type 2 (PH2) within 36 hours of treatment combined with neurological deterioration leading to an increase of ≥4 points on the NIHSS from baseline.
 
• Proportion of patients with death due to any cause
 
• Proportion of patients with Modified Rankin Scale (mRS) 5-6 at 3 months (severe disability or death).
 
 
Exploratory outcomes
 
 
• Proportion of patients achieving reperfusion (>90% and >50%) at 24 hours post stroke
 
• Infarct growth at 24 hours
 
• Proportion of patients achieving recanalisation at 24 hours post stroke (CTA or MRA).
 
 |

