## **12.4 Interim/Safety analysis**

Two safety parameters (deaths and symptomatic hemorrhages within 36 hours of intervention) will be monitored by the Independent Data Safety Monitoring Committee (DSMC) after each 100 patients have been enrolled. If there are concerns about the safety of participants, DSMC will make a recommendation to the trial steering committee about continuing, stopping, or modifying the trial. To compare the safety of current best practice therapy versus IV tenecteplase, two safety parameters - mortality at three months and the incidence of symptomatic ICH within 36 hours of intervention, will be tested independently. The Haybittle-Peto procedure for generating early stopping boundaries will be used. A recommendation of early termination due to safety reasons will be considered by the DSMC if the corresponding Haybittle-Peto boundary ( $p=0.001$ ,  $Z=3$ ) at a given interim analysis is crossed.

No interim analyses for the primary outcome are planned apart from the analysis for the purposes of adaptive sample size re-estimation as per the “promising zone” methodology of Mehta and Pocock based on the data from the first 592 patients.

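### The sICH definition has no death limb, so a PH2 that leads to death with no NIHSS scored in between is not counted as sICH

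*Protocol*

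**What the plan says.** The Synopsis (Study endpoint) defines sICH as PH2 within 36 hours of treatment with "neurological deterioration leading to an increase of ≥4 points on the NIHSS from baseline". Section 12.2 (Safety) repeats the requirement, "combined with neurological deterioration leading to an increase of" at least 4 points, and allows a second reference value: "or the lowest NIHSS value between baseline and 24 hours". Neither version names death.

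Section 12.4 gives sICH a formal monitoring role: "Two safety parameters (deaths and symptomatic hemorrhages within 36 hours of intervention) will be monitored", and this happens "after each 100 patients have been enrolled". It then says that "mortality at three months and the incidence of symptomatic ICH within 36 hours of intervention, will be tested independently". The boundary is stated as p=0.001, Z=3: "A recommendation of early termination due to safety reasons will be considered by the DSMC if the corresponding Haybittle-Peto boundary" is crossed. Section 12.4 gives no wider definition of symptomatic haemorrhage.

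NIHSS is scheduled at baseline and at 24 hours (sections 7.2.2 and 7.3, Appendix 1). Section 7.2.1 asks for close neurological observation, mainly over the first 48 hours, under local practice. No NIHSS is required when a patient deteriorates.

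**The concern.** The only clinical criterion is a measured NIHSS rise. A patient with a PH2 on imaging who then dies may have no score that shows the rise. This can happen when death comes before the 24-hour assessment, or when the bleed follows that assessment and death comes before anyone scores again. Such a patient has had the most severe deterioration possible, yet does not meet the stated definition.

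sICH is the bleeding-specific safety outcome, and section 12.4 tests it separately from mortality. Part of the control arm may receive no thrombolytic, so this parameter is the more direct signal of treatment-related bleeding. Losing even a few fatal events from a rare-event comparison reduces the absolute difference and the chance of seeing it.

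**Working it through.** **Reading the rule.** Take a patient with PH2 on imaging within 36 hours who dies of it, with no NIHSS between deterioration and death.

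1. PH2 within 36 hours: met.
2. NIHSS rise of at least 4 points from baseline (Synopsis), or from baseline or the lowest value to 24 hours (section 12.2): no post-bleed score exists, so it is not met under either version.
3. Death as an alternative, or an NIHSS value assigned at death: not in the Protocol.
4. Result: not an sICH in section 12.2, and not an event for the sICH parameter in section 12.4.
5. The same patient counts in all-cause death and mRS 5-6 (section 12.2) and in three-month mortality (section 12.4).

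If an unscheduled NIHSS before death shows the rise, step 2 is met and the bleed counts.

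**Size.** The Protocol gives no sICH rate, so there is no planned figure to reproduce. The 370 per arm comes from section 12.3. Every sICH rate, count and lost share below is an assumption.

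Pooled two-proportion statistic: Z = (p1 − p2) / √[p(1 − p)·2/n], with p the mean of p1 and p2 and n = 370.

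| Assumed situation | Recorded rates | Difference (points) | Risk ratio | Z |
|---|---|---|---|---|
| All bleeds counted | 6.0% vs 3.0% | 3.0 | 2.0 | 0.030/√(0.045·0.955·2/370) = 1.97 |
| 20% lost in both arms | 4.8% vs 2.4% | 2.4 | 2.0 | 0.024/√(0.036·0.964·2/370) = 1.75 |
| 40% lost on tenecteplase, 20% on control | 3.6% vs 2.4% | 1.2 | 1.5 | 0.012/√(0.030·0.970·2/370) = 0.96 |

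Equal loss weakens the signal without changing the risk ratio. Most of the fall to 0.96 comes from the assumed inequality of loss. None of the three values is near Z=3.

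**Near the boundary.** These counts were chosen to lie close to it, with three tenecteplase-arm bleeds uncounted:

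- 150 per arm: 14 vs 1 gives Z = 3.44; 11 vs 1 gives Z = 2.95.
- 296 per arm: 18 vs 3 gives Z = 3.33; 15 vs 3 gives Z = 2.87.

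**Chance of crossing Z=3 at a single look.** With 296 per arm and assumed true rates of 8% vs 2%, the probability is Φ[(p1 − p2 − 3·SE0)/SE1], where SE0 is the pooled and SE1 the unpooled standard error. It is 64% with all events counted, and 57%, 49% and 41% with 10%, 20% and 30% lost in both arms.

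**The case against.** The strongest reply is that few patients are affected and that their deaths are already monitored. A bleed must be imaged to be classed as PH2. Section 7.2.2 anticipates extra CT when neurological status changes, and section 7.2.1 asks for close observation, so many such patients will have an NIHSS before death. The wording in section 12.2 about the lowest value up to 24 hours itself presupposes scores beyond the scheduled ones. Mortality is the other stopping parameter, the board sees unblinded grouped data (section 8.5), and under section 12.4 it may recommend action on any safety concern. All of this stands, and it limits the size of the problem. It does not change how the definition classifies the remaining patients, and in the mortality count fatal bleeds are mixed with deaths from the stroke.

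A second reply is that a statistical analysis plan or adjudication charter could assign a maximal NIHSS at death. That is possible, and neither document is shown. But the Protocol states the definition itself, so this is wording already fixed and not detail left open. The plan is due only before data lock (section 12.5), which could be after many of the safety reviews.

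A reader might infer that the worst bleeds as a group drop out of safety monitoring, or that the comparison is necessarily biased toward no difference. The documents support neither. Only fatal PH2 bleeds with no intervening NIHSS are lost, and only from the sICH count. Bias in the risk ratio, the Protocol's effect measure, needs unequal loss between arms, which nothing in the Protocol establishes.

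**Conclusion.** The point holds in limited form. As written, the sICH outcome and the sICH stopping parameter omit any PH2 within 36 hours that leads to death without an NIHSS scored between deterioration and death. The deaths remain in all-cause mortality, mRS 5-6 and the mortality stopping parameter.

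The size cannot be determined from the Protocol. On assumed rates of 6% vs 3%, an equal 20% loss costs about 0.2 in Z (1.97 to 1.75) with no change in the risk ratio. A larger effect needs unequal loss or counts that happen to lie near the boundary, and both are assumptions. It would go too far to say that the stopping rule fails: the boundary prompts a recommendation, and the board can act without it.

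**What to change.** Use one sICH definition in the Synopsis and section 12.2: PH2 within 36 hours with deterioration giving an NIHSS rise of at least 4 points, or leading to death. In the same edit, reconcile the reference NIHSS, which is baseline only in the Synopsis and baseline or the lowest value to 24 hours in section 12.2. State in section 12.4 that its sICH parameter uses this definition.

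The cost is a few words in the Protocol and on the adjudication form. The blinded adjudicator must judge whether the death followed from the PH2, and the reported sICH rate may be slightly higher.
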